### Statistical analysis

An independent statistician will perform statistical analysis using SAS 9.3. The full analysis set population includes all randomized participants as allocated. Only missing data regarding the primary outcomes will be adjusted using the last observation carried forward method. The per-protocol population includes only patients who fulfil the protocol. Analysis of efficacy will be performed based on the full analysis set and per-protocol population. Safety analyses will be performed in those populations, which include all randomized participants who receive at least one spray of medication and who have at least one visit for safety, whether or not they are withdrawn prematurely.

A fully specified statistical analysis plan will be written before unmasking. Quantitative variables will be described as mean ± standard deviation or median, and qualitative variables as frequency and percentage. Baseline analyses will be performed using analysis of variance (ANOVA) or rank-sum test for quantitative data and chi-squared or Fisher’s exact test for qualitative data. A non-inferiority test will be used to compare the two active QWQYA groups, and a superiority test to compare the current-propellant QWQYA group and the placebo group. A one-sided confidence interval method will be used in efficacy analyses. Statistical significance will be considered for *P* ≤ 0.05.

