Owing to a lack of proven effective and safe therapies in Western medicine, an increasing number of patients turn to complementary and alternative medicine [13–15], including traditional Chinese medicine, for relief of symptoms of acute pharyngitis. In traditional Chinese medicinal theory, acute pharyngitis falls into the disease category of pharyngitis (houbi in Chinese Pinyin), and is mainly caused by external causes, including wind and heat. Based on traditional Chinese medicinal clinical practice, wind-heat syndrome and lung-stomach excess-heat syndrome are the most common syndromes. Of these, lung-stomach excess-heat syndrome is more common in patients, with underlying heat in the lungs and stomach, and is primarily characterized by sore throat, cough, dryness of throat, thirst, and fever. The general traditional Chinese medicinal therapeutic principle is to clear away heat and toxins, and to relieve the sore throat.

Although traditional Chinese medicine has been widely used in China for the treatment of acute pharyngitis for thousands of years, Chinese herbal medicine is not recommended for use as an effective therapy, owing to the lack of high-quality clinical trials in this area [16]. Qi-Wei-Qing-Yan aerosol (QWQYA) is a registered herbal prescription in China and manufactured by Shandong Bencao Pharmaceutical Co., Ltd (Shandong, China). Table 1 lists the detailed formula. Despite the use of QWQYA in acute pharyngitis for several years, its efficacy has never been investigated through a placebo-controlled trial. Moreover, dichlorodifluoromethane (CFC-12), the previous propellant of QWQYA, has gradually been banned by the Ministry of Environmental Protection of the People’s Republic of China, owing to its ozone-depleting properties [17]. Alternatively, 1,1,1,2-tetrafluoroethane (HFC-134a) is used as the current aerosol propellant, owing to its negligible ozone depletion potential [18]. Accordingly, the safety of QWQYA with the current aerosol propellant remains unknown.

**Table 1 Tab1:** Formula of Qi-Wei-Qing-Yan aerosol

Pinyin name	Botanical or zoological authority	Family name
Shandougen	*Euchresta japonica Hook. f. ex Regel*	Leguminosae
Shegan	*Belamcanda chinensis (L.) Redouté*	Iridaceae
Xuanshen	*Scrophularia ningpoensis Hemsl.*	Scrophulariaceae
Maidong	*Ophiopogon japonicus (L. f.) Ker-Gawl.*	Liliaceae
Chansu	*Bufo bufo gargarizans Cantor*	Bufonidae
Rengong Shexiang	*Moschus (Artificial)*	Not applicable

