Bingpian	*Dryobalanops aromatica Gaertn.f.*	Dipterocarpaceae

The objective of this trial is to evaluate the efficacy and safety of two QWQYAs (active medication with the current or previous propellant) in comparison with a placebo aerosol (placebo with the current propellant) in patients with acute pharyngitis (lung-stomach excess-heat syndrome). In this study, the investigators hypothesize that (1) time to complete resolution of sore throat will be shorter in the groups using QWQYA with the current or previous propellant; (2) the proportion of patients who achieve sore throat pain relief will be higher in the groups using QWQYAs; and (3) QWQYA with the current propellant will be safe.

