### Sample size calculation

The sample size was calculated on the basis of the two primary outcomes, using ‘Non-inferiority tests for two proportions [differences]’ in PASS 11.0. Based on a previous study [22], the mean time to complete resolution of sore throat in both active treatments was similar, both with a standard deviation of 2.2 days. A difference of 1 day or more between groups was regarded a clinically important effect. Setting a one-sided *α* of 0.05 and *β* of 0.1, the sample size was estimated to be 84 cases for each group. Based on consultation with clinical experts and a preliminary unpublished study provided by the sponsor, the relief rate of sore throat in QWQYA with previous propellant was estimated at 91 %, with a difference of 10 % or more considered clinically significant. The sample size was estimated at 118 participants for each group, assuming a one-sided *α* of 0.05 and *β* of 0.15. Both the sample sizes were calculated according to the formula:

*n* = $$ {\left[\frac{2\left({Z}_{1-\alpha /2}+{Z}_{\beta}\right)\sigma }{\delta -\varDelta}\right]}^2 $$

Therefore, the final sample size for each group was 118 participants. Taking approximate dropout rates of 20 % into account, the number of participants to be recruited was estimated at 140 per group. Therefore, a total of 420 patients will be recruited in this trial.

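### Both aerosols are hypothesised to beat placebo, but previous propellant versus placebo has no planned test, and the relief-rate sample size covers active-versus-active non-inferiority only

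*Protocol article*

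**What the plan says.** The last paragraph of the Background gives the objective as "to evaluate the efficacy and safety of two QWQYAs (active medication with the current or previous propellant) in comparison with a placebo aerosol". Hypothesis 1 is that "time to complete resolution of sore throat will be shorter in the groups using QWQYA with the current or previous propellant", and hypothesis 2 that "the proportion of patients who achieve sore throat pain relief will be higher in the groups using QWQYAs". Hypothesis 3 concerns the safety of the current-propellant product. None of the three mentions non-inferiority.

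The Statistical analysis section names two efficacy comparisons. One is between the actives: "A non-inferiority test will be used to compare the two active QWQYA groups". The other is against placebo, for one product only: "and a superiority test to compare the current-propellant QWQYA group and the placebo group". It names no third.

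The Sample size calculation section says that a PASS non-inferiority procedure for two proportions was used. For time to resolution it relies on earlier data in which "the mean time to complete resolution of sore throat in both active treatments was similar, both with a standard deviation of 2.2 days". For relief rate it takes 91% in the previous-propellant arm and a 10-point difference. It gives no placebo mean and no placebo relief rate.

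On the evidence so far, the Background says of QWQYA that "its efficacy has never been investigated through a placebo-controlled trial".

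**The concern.** The hypotheses and the tests do not line up, in either direction. The previous-propellant half of hypotheses 1 and 2 has no test. The comparison that sets the sample size, non-inferiority between the actives, corresponds to no stated hypothesis.

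This matters because of the reference arm. Non-inferiority shows that the new product is not much worse than the old one. It supports efficacy only if the old product works, and by the protocol's own account that has never been shown against placebo. The Discussion criticises earlier trials for using controls whose efficacy was not well established. Here a placebo arm is available to settle the question directly, but the plan does not use it for the reference product. Nor does the plan say that a non-inferiority result counts towards efficacy only if superiority over placebo has been shown.

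Finally, a reader who sees 85% power for relief rate in a placebo-controlled trial may take it as the power of the placebo comparison. It is not.

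**Working it through.** **Hypotheses against tests**

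| Contrast | In Background hypotheses | Planned test | Sized in the document |
|---|---|---|---|
| Current propellant v placebo | Yes | Superiority | No |
| Previous propellant v placebo | Yes | None | No |
| Current v previous propellant | No | Non-inferiority | Yes |

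**Inputs.** From the Sample size calculation section: relief rate 91%, difference 10 points, one-sided alpha 0.05, beta 0.15; SD 2.2 days, difference 1 day, one-sided alpha 0.05, beta 0.10; 140 recruited per group. Placebo rates and a placebo SD are not given, so every placebo value below is an assumption.

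**Step 1: reproduce 118 (relief rate).** Non-inferiority with no true difference and unpooled variance:

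n = (z₀.₉₅ + z₀.₈₅)² × 2p(1−p) / margin² = (1.645 + 1.036)² × 2(0.91)(0.09) / 0.10² = 117.8, so 118.

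This matches exactly. Read as superiority (91% v 81%), the same 10 points would need

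n = (1.645 + 1.036)² × [0.91(0.09) + 0.81(0.19)] / 0.10² = 169.5, so 170 per group.

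So 118 is an active-versus-active non-inferiority size.

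**Step 2: reproduce 84 (time to resolution).** n = 2(z₀.₉₅ + z₀.₉₀)² × SD² / 1² = 2(1.645 + 1.282)² × 2.2² = 82.9, so 83 by the normal approximation and 84 with the t distribution. With zero true difference, this is the same arithmetic as superiority for a true 1-day effect.

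**Step 3: superiority power, relief rate.** Power = Φ[(0.91 − p₀)/SE − 1.645], with SE = √{[0.91(0.09) + p₀(1 − p₀)]/n}. For p₀ = 0.81 and n = 118, SE = 0.0447 and power = Φ(2.237 − 1.645) = 0.72.

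| Assumed placebo rate | 118 per group | 140 per group (all randomised) |
|---|---|---|
| 86% | 33% | 37% |
| 81% | 72% | 79% |
| 76% | 94% | 96% |

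**Step 4: superiority power, time to resolution.** With placebo SD assumed 2.2 and a 1-day difference at n = 118, SE = 2.2√(2/118) = 0.286 and power = Φ(3.491 − 1.645) = 0.97. At n = 84 it is 0.90.

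**Step 5: chance of declaring non-inferiority on relief if all three arms share one rate p.** Φ[0.10/√(2p(1−p)/118) − 1.645] gives 85% at p = 91%, 62% at p = 81% and 51% at p = 70%.

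**The case against.** - **The placebo arm already protects the conclusion.** Current propellant is tested against placebo, and the Investigational medicinal product section gives both actives the same active solution and excipients. If neither spray worked, the superiority test would normally fail. This stands in part. A reader might infer that non-inferiority could pass unchecked, or that previous versus placebo is the only possible evidence on the reference. Neither follows, because the current-versus-placebo test gives indirect evidence. But the plan does not make non-inferiority depend on that test, and the test does not answer the previous-propellant hypothesis.
- **Two ineffective sprays would not be declared non-inferior 85% of the time in general.** Correct. That figure requires a placebo relief rate of 91%, and it falls to 62% and 51% at common rates of 81% and 70%.
- **The placebo comparison is not shown to be underpowered.** Correct. A reader might infer a general shortfall, but the document gives no placebo rate and the result for relief depends on it. The 10 points are the margin used for sizing, not a predicted effect over placebo. For time to resolution, a 1-day effect has ample power if the placebo SD is similar. What stands is that superiority on relief was not sized.
- **A later statistical analysis plan may add the test.** It may, since the protocol promises one before unmasking, and testing order is often settled there. But the hypotheses and the list of comparisons conflict within this document.
- **The word "or" in hypothesis 1 could mean either propellant.** Possible, but hypothesis 2 uses the plural and the objective sets both products against placebo.

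**Conclusion.** The mismatch is real and should be fixed. One of the two hypothesised placebo contrasts has no planned test, the non-inferiority comparison has no stated hypothesis, and the non-inferiority claim is not conditional on any active arm beating placebo, although the reference has no earlier placebo-controlled evidence.

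On size, the 118 per group with 85% power applies to active-versus-active non-inferiority on relief rate and to nothing else. Superiority power on relief runs from 33% to 94% at 118 per group (37% to 96% at 140) over assumed placebo rates of 86% down to 76%, with 91% on active and one-sided 0.05. No shortfall is shown for time to resolution, provided that the placebo SD is near 2.2 days. The planned test of the current product against placebo is unaffected, and the repair needs no new data. The point is therefore a correction to make before unblinding, not a fatal flaw.

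**What to change.** 1. In Statistical analysis, add a superiority test of previous propellant versus placebo on the primary outcomes. State a fixed order: current v placebo, previous v placebo, then current v previous non-inferiority. Say that non-inferiority is read as evidence of efficacy only if superiority over placebo has been shown.
2. Alternatively, restrict the efficacy objective and hypotheses in the Background to the current propellant. Still make the efficacy reading of non-inferiority conditional on current propellant beating placebo.
3. In either case, add the non-inferiority hypothesis to the Background.
4. In Sample size calculation, say that the 85% for relief rate refers to non-inferiority only. Give superiority power over a range of placebo rates marked as assumptions, as in the table above, rather than a single figure.

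The cost is wording and, under the first option, one more contrast from data that the three-arm design already collects. No patients or visits are added. The downside is that the non-inferiority claim becomes conditional and could be lost if an earlier test in the sequence fails.

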### Ethical considerations and dissemination

The study protocol has been reviewed and approved by the Biomedical Ethics Committee of West China Hospital of Sichuan University (Chengdu, China). Any modifications, including the principal investigator, study protocol, and informed consent forms must be re-submitted, reviewed, and approved by the Biomedical Ethics Committee. Trained research investigators will explain the study procedures using information sheets, which will be provided to all potential participants prior to participation. All participants must voluntarily give their written, informed consent prior to any study procedures. Participants with impaired decision-making capacity who might have difficulty weighing the risks and benefits of the study will be excluded from this study. The principal investigator, sponsor, ethical committees, and drug regulation agencies have access to individual patient’s data, and no ancillary studies will use these participants’ data. Moreover, each patient will be identified with a unique identity without any other personal identifier for purposes of maintaining confidentiality. This study protocol has been prepared according to the SPIRIT checklist [23].

Additionally, chest X-rays will be obtained in selecting eligible participants, to exclude patients with lower respiratory tract infection, and a urine pregnancy test (strip) will be used to detect early suspected or unknown pregnancy in women with child-bearing potential.

A preliminary study (an unpublished observation by [name]) suggests that QWQYA might be associated with a risk of mild reduction of heart rate within normal range. However, another two trials [24, 25] did not find any such association. In this study, myocardial markers will be tested and electrocardiography will be performed in potential participants, and a detailed history will be taken, to exclude those with an underlying heart disease. In addition, the test of myocardial markers and electrocardiography will be performed again after treatment to monitor participants for potential adverse effects.

The results of this study will be presented at national or international conferences and submitted to peer-reviewed journals.

## Discussion

A Cochrane review [16] of 12 randomized controlled trials that assessed the efficacy and safety of Chinese herbal medicine for sore throat found that trials in this area were methodologically of poor quality, with controversial and questionable evidence of efficacy. Moreover, the randomized controlled trials included in this review and trials conducted thereafter [26–28] all used a ‘positive effect drug’ as a control, comparing the Chinese herbal medicine under investigation with another Chinese herbal medicine or a Western medicine. However, the efficacy of these ‘positive effect drugs’ has not yet been well established. To the best of our knowledge, this will be the first multicenter, double-blind, randomized, placebo-controlled trial of Chinese herbal medicine designed to treat acute pharyngitis in an adult population. Not only might it establish the basis for the efficacy and safety of QWQYA in the treatment of acute pharyngitis, but it might also provide evidence regarding Chinese herbal medicine for treating acute pharyngitis and an alternative treatment option for the management of acute pharyngitis.

This trial is placebo-controlled and focuses on viral pharyngitis in adults. Although it is not always easy to distinguish viral from bacterial causes, laboratory confirmation of bacteria, including a rapid antigen detection test and throat culture is not indicated and recommended in adults with a lower likelihood of GABHS infection [29]. In this trial, Centor criteria (a history of fever, tonsillar exudates, tender anterior cervical adenopathy, and lack of cough) will be applied to exclude patients with potential GABHS pharyngitis, with the absence of three or four of the criteria indicating a negative predictive value of more than 80 % [30, 31].

It is well-known that the gold standard for assessing the efficacy of specific intervention is a randomized placebo-controlled trial. Ideally, a placebo should be an inactive substance that is pharmacodynamically inert. However, it is significantly difficult to develop appropriate placebos, in terms of smell, taste, and color, in clinical trials of herbal medicine especially those of compound formula in a liquid form. To our knowledge, no validated placebo of Chinese herbal medicine has been developed in the setting of acute pharyngitis. Moreover, several clinical trials outside the setting of acute pharyngitis have applied 10–20 times dilutions of active herbs as placebos in China and Japan [32, 33]. In this trial, one-twentieth of the total dose of active solution is used as the placebo, since it is assumed to be unlikely that a tiny amount of 14.4 mg per day could be an effective treatment. Both the active aerosols and the placebo aerosol are issued in bottles identical in size, shape, and color, to ensure appropriate blinding. In addition, participants are required not to communicate with each other, to minimize the possibility of revealing differences between the placebo and active medication.

### Trial status

This trial is preparing for patient recruitment at the time of manuscript submission.

## Abbreviations

ANOVA: analysis of variance
GABHS: Group A beta-hemolytic streptococcal
QWQYA: Qi-Wei-Qing-Yan aerosol
